### Sample size calculation

The trial is designed with regards to the primary outcome. The sample size calculation is based on a pilot study performed at our department that included 18 patients with constrained Lubinus cups (anti-dislocation ring) and 174 patients with uncontrained Lubinus cups [25]. All patients received a THA due to a pathologic fracture or an impending pathologic fracture because of MBD. The patients with a constrained Lubinus cup had a 1-year dislocation rate at 0%, while those with an unconstrained Lubinus cup had a 7% 1-year dislocation rate. Based on this, we decided on a non-inferiority margin with a 6% absolute risk-difference, as dislocation rate outside of this margin would place DM in the same range as unconstrained THA, which is considered inferior to CL and DM. We expect that the probability of avoiding hip dislocation within 6 months is 99% for CL and 98% for DM. With power at 80% for a one-sided 95% confidence interval, we calculate that a minimum of 73 patients is required in each treatment group for a binary-outcome non-inferiority trial. We will therefore enroll a minimum of 73 patients in each treatment arm amounting to minimum of 146 patients in total.

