
## Methods and design

### Study design and objectives

The current study is investigator initiated and designed as a randomized, two-arm, open-label non-inferiority study. The study is a single-center study performed at the Musculoskeletal Tumor Section at the Department of Orthopedic Surgery, Rigshospitalet, Denmark. Patients will be stratified by whether subtrochanteric bone resection is performed and randomly allocated to either CL or DM in a 1:1 ratio. The primary objective is to assess whether DM is non-inferior to CL regarding the post-operative joint dislocation risk. Secondary objectives include the overall survival, implant survival, the post-surgery complication rate, investigator reported outcomes, and patient reported outcomes (see the “ Outcome measures” section).

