### Data analysis

Data analysis will be performed both per protocol and on an intention to treat basis. Data analysis will be performed blinded to treatment allocation. We will analyze non-inferiority with the fixed-margin method. We will use a pre-defined non-inferiority margin with a 6% absolute risk difference in this trial. We will conclude non-inferiority of DM compared to CL if the estimated one-sided 95% confidence interval of the difference in cumulative incidence lies entirely below this margin.

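### 73 patients per arm cannot give 80% power at a 5% one-sided error rate: the figure comes from a normal approximation applied to about two expected dislocations

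*Protocol article*

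**What the plan says.** Sample size calculation in the protocol article gives all the design inputs. The planning rates are in this sentence: "We expect that the probability of avoiding hip dislocation within 6 months is 99% for CL and 98% for DM". The margin is an absolute difference of 6 percentage points ("we decided on a non-inferiority margin with a 6% absolute risk-difference"). The target and the result are stated together: "With power at 80% for a one-sided 95% confidence interval, we calculate that a minimum of 73 patients is required in each treatment group", or 146 in total. Allocation is 1:1 (Study design and objectives). No inflation is made for loss to follow-up, because hospital records are expected to give dislocation status for every patient (Study withdrawal and replacement).

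Data analysis sets the decision rule. Non-inferiority is concluded "if the estimated one-sided 95% confidence interval of the difference in cumulative incidence lies entirely below this margin". Neither section names the sample-size formula or the type of interval, and neither mentions how few events are expected.

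**The concern.** With dislocation rates of 1% and 2%, 73 patients per arm should produce about two dislocations in the whole trial. A normal approximation to a difference of proportions is unreliable there. An arm with no events adds no variance to a Wald or Greenwood-type interval, so the upper limit comes out too low and non-inferiority is declared too readily.

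Two things are at stake. If the analysis uses the method that generated the sample size, a DM cup that is truly worse by the full margin passes at more than twice the stated rate. The protocol itself places a cup outside that margin in the range of unconstrained THA. If the analysis uses an interval that holds its error rate, the trial is much less likely to succeed than its readers and funders have been told.

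**Working it through.** **Inputs (all from the protocol article).** Dislocation rates: CL 1%, DM 2%. Margin: 6 points. One-sided error 5% (z = 1.645), power 80% (z = 0.842). Allocation 1:1, no dropout.

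**1. Reproducing 73.** Unpooled (Wald) formula:

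n = (1.645 + 0.842)² × (0.01×0.99 + 0.02×0.98) / (0.06 − 0.01)² = 72.95, rounded up to 73.

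The protocol names no formula. That this one was used is inferred from the exact match. A one-sided 2.5% level would give 93, so 5% was used.

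**2. Expected events.** CL: 73 × 0.01 = 0.73. DM: 73 × 0.02 = 1.46. Total 2.19.

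- P(no CL event) = 0.99^73 = 0.480
- P(no DM event) = 0.98^73 = 0.229
- Both arms empty: 0.480 × 0.229 = 11%
- At least one arm empty: 0.480 + 0.229 − 0.110 = 60%

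With no events in either arm the Wald upper limit is exactly 0, while the score limit is 3.6%.

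**3. Which results pass at 73 per arm.** Largest number of DM events that still gives an upper limit below 6%:

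| CL events | 0 | 1 | 2 | 3 |
|---|---|---|---|---|
| Wald | 2 | 2 | 2 | 3 |
| Score (Miettinen-Nurminen) | 1 | 1 | 2 | 2 |
| Exact unconditional | 0 | 1 | 2 | 2 |

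The Wald and score limits part mainly at two results. DM 2 vs CL 0: Wald limit 5.9% (pass), score 8.0% (fail). DM 2 vs CL 1: Wald 5.2% (pass), score 6.8% (fail). Under the planning rates these have probability 0.250 × 0.480 + 0.250 × 0.354 = 21%.

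**4. Power at 2% vs 1%.** P(DM = 0, 1, 2, 3) = 0.229, 0.341, 0.250, 0.121. P(CL = 0, 1, 2) = 0.480, 0.354, 0.129, so P(CL ≥ 2) = 0.166 and P(CL ≥ 3) = 0.037.

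- Wald: P(DM ≤ 2) + P(DM = 3) × P(CL ≥ 3) = 0.820 + 0.121 × 0.037 = 0.825
- Score: P(DM ≤ 1) + P(DM = 2) × P(CL ≥ 2) = 0.570 + 0.250 × 0.166 = 0.611; the remaining small terms bring it to 0.612

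**5. Error rate on the margin.** The same sums with DM at CL + 6 points:

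| True rates, DM vs CL | Wald | Score |
|---|---|---|
| 7% vs 1% | 11.2% | 4.6% |
| 6% vs 0% | 17.9% | 6.2% |

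At 6% vs 0% the CL arm is always empty, so the error is P(DM ≤ 2) for Wald and P(DM ≤ 1) for score. Newcombe and Farrington-Manning limits give the same figures as Miettinen-Nurminen at this size. The exact unconditional limit stays below 5% and has 44.8% power. One million simulated trials confirmed the Wald figures.

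**6. Could another interval do better?** The most powerful test with 5% error at 7% vs 1% alone (Neyman-Pearson) reaches 62.9% power. If the error must be at most 5% along the null boundary (CL rate 0 to 94%), a linear programme gives a ceiling of 59.7%. Both ceilings cover every test on the two arm counts.

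**7. What 80% would take.** The score limit has 81.5% power at 125 per arm (largest error 5.4%) and 80.2% at 130 (5.1%). The exact limit has 80.1% at 130.

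**8. Sensitivity to n.** Exact power is saw-toothed. The score limit has 45% power at 72 per arm, because DM 1 vs CL 0 no longer passes, then 61.2% at 73 and 57.9% at 80.

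**The case against.** The strongest reply is that the protocol's calculation is numerically correct and that the type of interval properly belongs to a statistical analysis plan, which is not shown. The document never says that a Wald limit will be used, so the 11% to 18% error rates describe an analysis nobody has specified. That is fair as far as it goes: leaving the interval unnamed is not itself the fault. The power statement, however, is in the protocol, and by step 6 no analysis plan can make it true at the stated error rate.

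Three further objections concern the remedy.

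- The score limit is not strictly a 5% procedure. It reaches 6.2% at 6% vs 0%, and 0% is the rate the pilot reported for constrained cups. This stands; a strict guarantee means the exact limit and about 45% power.
- The figure of 61% belongs to exactly 73 per arm. This also stands. The protocol calls 73 a minimum, and a per-protocol set could be smaller, so the restated power should be tied to its n.
- Cumulative incidence equals a simple proportion only with complete follow-up. The protocol expects complete dislocation data from hospital records, so the premise is the protocol's own. It would need revisiting if withdrawals left status unknown for some patients.

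**Conclusion.** The concern holds. At 73 per arm, the stated 80% power and the stated 5% one-sided error cannot both be true under the protocol's own planning rates. A Wald limit gives 82.5% power with 11.2% error at 7% vs 1%. Limits that keep the error near or below 5% give 45% to 61% power, and the ceiling for any test with 5% error at 7% vs 1% is 62.9%. The choice of interval alone would change the primary conclusion in about 21% of trials.

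These figures assume independent binomial counts, true rates of 2% and 1%, a common rate across strata, and known 6-month status for all 146 patients. The use of the Wald formula is an inference from the match at 72.95, but the power ceiling does not depend on it.

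**What to change.** **Data analysis.** Name the one-sided 95% Miettinen-Nurminen (score) upper limit for the 6-month risk difference, stratified by subtrochanteric resection, as the decision interval. State that Wald and Greenwood limits will not be used for the decision. Do this before any comparison of the arms. The stratified version also has about 61% power across several stratum splits.

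**Sample size calculation.** Keep 146 patients and restate the power as about 61% for 99% vs 98% dislocation-free with this interval. Say that the figure holds at 73 evaluable patients per arm and falls to 45% at 72. Disclose that the error rate can reach 6.2% when the CL rate is near zero.

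**Cost.** Two amended statements and a less favourable power figure, with no extra patients. If the sponsor wants a true 80%, the protocol sets 73 only as a minimum; about 125 to 130 per arm would be needed, which is 52 to 57 more in each arm.

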### Data analysis

Data analysis will be performed both per protocol and on an intention to treat basis. Data analysis will be performed blinded to treatment allocation. We will analyze non-inferiority with the fixed-margin method. We will use a pre-defined non-inferiority margin with a 6% absolute risk difference in this trial. We will conclude non-inferiority of DM compared to CL if the estimated one-sided 95% confidence interval of the difference in cumulative incidence lies entirely below this margin.

## Discussion

To our knowledge, this study is the first randomized trial to compare DM and CL in patients with MBD. Patients with MBD of the hip have an increased risk for adverse events and post-surgical complications. The current study aims to improve our knowledge in selecting the right joint solution for this vulnerable patient-population.

### Risk assessment and ethical considerations

THA is a well-established and commonly performed procedure, performed in thousands of patients each year in Denmark. Both acetabular solutions in this study are currently in use in our department but are currently selected at the discretion of the operating surgeon. THA, as with any other surgery, is associated with the risk of bleeding, wound infections, deep venous thrombosis, neurovascular injury, or death. Furthermore, there is also the risk of THA-related complications such as hip dislocation, limb-length discrepancy, and aseptic loosening of the inserted implant. However, all subjects included in this study have been offered surgery after a careful review by an interdisciplinary board of specialists that has determined that the benefits from surgery outweigh the risks. All surgeries will be performed at a highly specialized tertiary center, by orthopedic surgeons experienced with orthopedic oncology and the specific prosthesis used in this study. The current study is approved by the Scientific Ethical Committee of the Capital Region of Denmark (H-21078128), the Danish Data Protection Agency (P-2022–124), and has been registered at ClinicalTrials.gov (NCT05461313). All patients will receive thorough oral and written information about the project, and written informed consent will be obtained before the commencement of any study-related procedures. The patients will furthermore be informed that participation is voluntary, that they can freely decline study participation, and that they have the right to withdraw from the study at any time and for any reason without prejudice to current or future medical care at the institution.

### Clinical implications and future directions

This study is the first randomized trial to investigate how the type of articulating surface affects the post-operative joint-dislocation rate in patients with MBD, which are considered a high-risk population regarding post-operative dislocation, while also providing important evidence on the safety and post-operative complication rate in patients with MDB who receive a THA. Future studies should investigate which of CL or DM is superior if non-inferiority is concluded. Furthermore, future randomized trials are needed to determine whether certain articulating bearings should be preferred in patients with subtrochanteric resections compared to patients without subtrochanteric resections or in patients with isolated femoral metastases compared to patients who also have acetabular involvement.

## Trial status

All relevant regulatory approvals have been obtained. The trial is ongoing. The first subject was recruited on September 20, 2022.

## Data Availability

Only study investigators declared in this protocol will have access to the data from this trial. Access can be granted to other researchers in an anonymized form upon a reasonable request.

## Abbreviations

CL: Constrained acetabular liner
DM: Dual mobility cup/dual mobility liner
Eq-5d: European quality of life—5 dimensions questionnaire
HHS: Harris hip score
MBD: Metastatic bone disease
MSTS: Musculoskeletal tumor society score
TESS: Toronto Extremities Salvage Score for the lower extremity
THA: Total hip arthroplasty
